#### Description of baseline characteristics and homogeneity of the two groups

To describe the baseline characteristics of continuous data, the mean ± SD, or range with minimum and maximum, will be used. In the case of dichotomous data, the frequency will be reported as a percentage. To evaluate the homogeneity of the baseline characteristics between the two groups, a two-sample t test for continuous data and the *χ*^2^ test for dichotomous data will be carried out. If there is a significant difference between the two groups in terms of baseline characteristics, we will use analysis of covariance (ANCOVA) or logistic regression.

#### Primary outcome

The primary outcome—PR after 6 weeks of EA—will be compared between the groups using the *χ*^2^ or Fisher’s exact test.

#### Secondary outcomes

The independent t test will be used to evaluate changes in the NDI-K score after 6 weeks of treatment. If there is a covariate at baseline, an ANCOVA will be performed. To compare variables between the two groups, the two-sample t test will be used for parametric analyses, and the Mann-Whitney U test, for nonparametric analyses.

A repeated measures analysis of variance or repeated measured ANCOVA will be used to analyze group-by-time interactions, as well as intergroup differences. The *χ*^2^ test or Fisher’s exact test will be used to analyze nominal variables in each group as well as to compare AEs between groups.

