#### Randomization and allocation concealment

Sixty participants will be randomly assigned to either the EA or sham EA group. A random number table will be generated using block randomization with blocks of four by R for windows 3.2.1 (R Foundation for Statistical Computing, Vienna, Austria); to this end, the block randomization function will be used with blocks of four. The allocations will be kept sealed in a double-locked cabinet by an independent statistician. If the participants pass the screening test, they will be allocated according to the procedure above to conceal the allocation from both investigators and participants. After allocation, the statistician will email a unique random number and participant group allocation to both the clinical research coordinator and the Korean medicine doctors (KMDs). This feedback document will be kept in the master file for the trial.

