#### Secondary outcomes

##### Nepean dyspepsia index - Korean version

The Nepean dyspepsia index (NDI), a disease-specific instrument used to assess GERD symptoms [31], is a reliable and valid questionnaire [32, 33]. In this trial, the Korean version of NDI (NDI-K) will be used. It was validated in 2004 by Lee et al. [34] and contains 40 items comprising two sections: symptom-based questions (duration, severity, and degree of 15 separate symptoms), and those pertaining to the quality of life (QoL). The patient will complete the questionnaire at baseline, visit 6, and visit 12.

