### Sample size calculation

The required sample size was calculated on the basis of the difference in PR between the EA and sham EA groups. On the basis of previous research [55], we assumed the PR would be 92.8 % in the treatment group and 57.1 % in the control group. With a 5 % false positive error (*α* = 0.05, two-sided) and 80 % power (*ß* = 0.2) the required sample size in each group was *n* = 21.9. Assuming a 25 % of dropout rate, the real-world sample size will be *n* = 30 in each group, for a total of 60 participants.

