### Statistical analysis

An independent statistician blinded to group allocation will carry out the statistical analysis using SPSS™ 18.0 (SPSS Inc., Chicago, Illinois, USA). All final data will be securely stored, and only the statistician will have access. We will perform both intention-to-treat (ITT) and per protocol (PP) analysis, with all analyses being based on the ITT principle. Any participant who receives EA more than nine times during the study period will be eligible for PP analysis.

For ITT analysis of secondary outcomes, we will use the “last observation carried forward” rule. In the case of the primary outcome, however, missing values will not be replaced, because of the characteristics of adequate relief (AR). We will only count actual responses regarding AR. When AR occurs in more than 50 % of the treatment sessions in which a study subject participated, the participant will be classified as a responder. All data will be shown as the mean ± standard deviation (SD) or as numbers and percentages. The statistical significance level will be set at 0.05 (two-sided), with 95 % confidence intervals (CI). The analysis for safety will also follow the principles of ITT.

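### The NDI-K analysis defaults to a t test on change and adjusts for baseline only after a significant baseline difference, which gives up precision on a secondary outcome at no benefit

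*Protocol article*

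**What the plan says.** In the protocol article, Statistical analysis, Secondary outcomes, the NDI-K comparison is stated as: "The independent t test will be used to evaluate changes in the NDI-K score after 6 weeks of treatment". The next sentence makes adjustment conditional: "If there is a covariate at baseline, an ANCOVA will be performed". That sentence names no covariate. The preceding subsection on baseline characteristics and homogeneity shows how the condition is meant to work. Groups are compared at baseline by t tests and χ² tests, and ANCOVA or logistic regression is used "If there is a significant difference between the two groups in terms of baseline characteristics".

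The baseline score is available for everyone. The NDI-K description says "The patient will complete the questionnaire at baseline, visit 6, and visit 12", and Table 2 has NDI-K at V1.

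The same statistical subsection adds two general provisions: a two-sample t test or Mann-Whitney U test for comparing variables between the groups, and repeated measures ANOVA or ANCOVA for group-by-time interaction and differences between groups. Neither commits to adjusting for the baseline score.

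**The concern.** A change score uses the baseline value only by subtracting it, which fixes its coefficient at 1. ANCOVA estimates that coefficient from the data and so removes more residual variation unless the best coefficient happens to be 1. When the correlation is moderate, subtraction over-corrects. A participant with a high baseline score then tends to show a larger fall through regression to the mean, and any chance imbalance feeds into the estimate.

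A significance test at baseline is a poor gate for adjustment. In a randomised trial it is met by chance, and imbalances that fall short of significance stay unadjusted. With 30 per arm, and a sample size set on the responder outcome alone, NDI-K has no planned power margin. What is at stake is the width of the confidence interval and the power for this outcome.

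**Working it through.** **The plan's own figure.** The article gives no power, SD or correlation for NDI-K. Its only sample-size figure is for the responder proportion: "we assumed the PR would be 92.8 % in the treatment group and 57.1 % in the control group", two-sided α = 0.05, 80% power.
- Mean proportion = (0.928 + 0.571)/2 = 0.7495.
- Pooled-variance formula: n = [1.96·√(2 × 0.7495 × 0.2505) + 0.8416·√(0.928 × 0.072 + 0.571 × 0.429)]² / 0.357² = 21.91 per group, against 21.9 stated.
- With 25% dropout: 21.9/0.75 = 29.2, taken to 30.

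The figure reproduces, and it fixes 30 per arm for what follows.

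**Variance of the two analyses.** Let s0 and s1 be the SDs at baseline and week 6, and r their within-group correlation.
- Change score: s0² + s1² − 2r·s0·s1.
- ANCOVA: s1²(1 − r²).
- Difference: (s0 − r·s1)², which is never negative and is zero when s1/s0 = 1/r.

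So the direction does not depend on the unknown values, apart from the degree of freedom that ANCOVA spends: a factor of about 1 + 1/(2 × 30 − 4) = 1.018.

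**Size with equal SDs (assumed).** The ratio is (1 − r²)/(2(1 − r)) = (1 + r)/2. The last column starts from an effect with 80% power under the t test, by normal approximation.

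| r (assumed) | Variance ratio | With df penalty | CI narrower by | Equivalent n per arm | Power under ANCOVA |
|---|---|---|---|---|---|
| 0.3 | 0.65 | 0.66 | 19% | 46 | 93% |
| 0.5 | 0.75 | 0.76 | 13% | 40 | 90% |
| 0.7 | 0.85 | 0.87 | 8% | 35 | 86% |
| 0.9 | 0.95 | 0.97 | 2.5% | 32 | 82% |

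**Size with unequal SDs.**
- s1/s0 = 1.5, r = 0.5: change 1 + 2.25 − 1.5 = 1.75; ANCOVA 2.25 × 0.75 = 1.6875; ratio 0.96, a gain of about 4%.
- s1/s0 = 1.3, r = 0.7: change 1 + 1.69 − 1.82 = 0.87; ANCOVA 1.69 × 0.51 = 0.862; ratio 0.99, a gain of about 1%, which the degree-of-freedom penalty cancels.
- A smaller SD at week 6 enlarges the gain.

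**Effect of last observation carried forward.** As an upper-bound illustration, suppose all 25% of dropouts leave before the mid-treatment assessment and carry their baseline forward, with equal SDs and no mean shift. Then r = 0.5 becomes 0.75 × 0.5 + 0.25 × 1 = 0.625, the ratio is 1.625/2 = 0.81, and the gain falls from 25% to about 19%.

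**What the conditional rule recovers.** This was simulated with 20,000 trials per setting, 30 per arm and equal SDs, using ANCOVA only if baseline NDI-K differs at p < 0.05. The trigger was met in about 5% of trials.

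| r | Power: t test | Power: conditional rule | Power: always ANCOVA | Type I error: conditional rule |
|---|---|---|---|---|
| 0.3 | 0.79 | 0.80 | 0.92 | 0.042 |
| 0.5 | 0.79 | 0.80 | 0.88 | 0.045 |
| 0.7 | 0.79 | 0.79 | 0.84 | 0.048 |

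Because the rule acts on the largest imbalances, it does reduce the spread of the estimate somewhat. At r = 0.3 the empirical SD is 0.305 for the t test, 0.292 for the rule and 0.249 for ANCOVA, so the rule achieves (0.305² − 0.292²)/(0.305² − 0.249²) = 0.25 of the variance reduction. Almost none of that reaches the test, as the power columns show. Type I error was about 0.05 for both the t test and always-ANCOVA.

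**The case against.** The strongest reply is that nothing here is invalid. The t test on change is unbiased under randomisation and holds its error rate, NDI-K is secondary, and no power was claimed for it. All of that stands, and it limits the point to efficiency.

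The size is also open. The 35%, 25% and 15% figures need equal SDs as well as an assumed r, and the article gives neither. A larger SD at week 6 could remove most of the gain, and carrying observations forward would tend to reduce it. That stands too, so the idea that ANCOVA is worth one third more patients (30 to 40 per arm at r = 0.5) is one point in a wide range.

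A reader might infer that the article leaves five interchangeable tests for NDI-K and so an open p-value. The text does not support this. It names the t test for NDI-K change, gives Mann-Whitney as a general nonparametric option, and directs the repeated measures models mainly at group-by-time interaction. Nor does the t test/ANCOVA rule inflate false positives, since its simulated type I error was 0.042 to 0.048. Selection among all the listed tests was not computed, so no claim is made about it.

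It could also be said that covariates belong in a statistical analysis plan that is not shown. Leaving the covariate unnamed is indeed no finding. The default test and the conditional trigger are stated in the article, however, and can be judged as they stand. The repeated measures ANCOVA does not answer the point, because it is offered as an alternative with no commitment to baseline adjustment.

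**Conclusion.** The point holds as a matter of efficiency on a secondary outcome. The stated default is valid but gives up precision that an already collected score would supply, and the significance trigger recovers almost none of the lost power. With equal SDs the variance reduction is about 35%, 25% and 15% at r = 0.3, 0.5 and 0.7, less about 2% for one degree of freedom. It may be only a few per cent, or nothing net, if scores spread out by week 6.

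The 5% trigger rate assumes that the baseline test in question is the one on NDI-K itself. A significant difference in some other characteristic would not clearly bring the baseline NDI-K score into the model.

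The responder analysis, the sample size of 60 and type I error are not affected. The change is worth making, but the trial's main conclusion does not depend on it.

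**What to change.** State that the main between-group analysis of NDI-K is ANCOVA of the week-6 score on treatment group and V1 score, fitted whatever any baseline test shows, and delete the conditional clause. Do the same for the other continuous secondary outcomes with a V1 value in Table 2: the 11-point numerical rating scale, KGSRS, EQ-5D, PSS, gastrin, motilin and the cytokines.

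The repeated measures analysis of group-by-time can stay as a supporting analysis that uses the visit 6 data, and a nonparametric comparison can stay as a sensitivity analysis. If hormones or cytokines are to be log-transformed, decide that in advance, not after inspecting the distributions.

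The cost is a change of wording and one degree of freedom per model. No new data or participants are needed.

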**Methods/design:**

This is a protocol for a randomized, patient-blinded, assessor-blinded, sham-controlled trial. Sixty participants with symptoms of gastroesophageal reflux disease, who have previously undergone standard treatment, will be recruited from August 2015 at Kyung Hee University Korean Medicine Hospital. The participants will be allocated to either the electroacupuncture (n = 30) or the sham electroacupuncture group (n = 30); the allocation will be concealed from both the participants and the assessors. The EA group will undergo penetrating acupuncture at 18 fixed points and two optional points chosen using the pattern identification for gastroesophageal reflux disease. Electrical stimulation will be applied at some of the acupoints. The sham electroacupuncture group will undergo nonpenetrating acupuncture without electrical stimulation at 18 nonspecific points, each of which will be only 2 cm away from the true acupoints used in the electroacupuncture group. In both groups, the procedure will be performed using the Park device. The treatment will last for 6 weeks (with two sessions each week), and the outcome will be evaluated at baseline, 3 weeks, and 6 weeks. The primary outcome will be the proportion of responders with adequate symptom relief, whereas the secondary outcomes will comprise the results of the Nepean dyspepsia index; the Korean gastrointestinal symptom rating scale; the EQ-5D™; levels of gastrin, motilin, and inflammatory cytokines; the perceived stress scale; the qi-stagnation questionnaire; the patient global impression of change; and the spleen qi deficiency questionnaire.

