### Hypothesis

Partially individualized EA treatment is superior to sham EA in terms of easing the symptoms of GERD.

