##### Gastrointestinal hormone (gastrin, motilin)

GERD is related to weakness in the lower esophageal sphincter [35], and motilin [36] and gastrin [37, 38] have been reported to increase strength of the lower ESP (LESP). Motilin is an endogenous gastrointestinal hormone that increases upper GI tract motility, and it is considered an endogenous prokinetic hormone [39]. Gastrin is also a gastrointestinal polypeptide; it is thought to stimulate the lower esophageal sphincter by increasing the LESP [40]. However, controversy exists regarding whether EA increases gastrin and motilin levels [11, 13–16], so we will attempt to confirm the influence of EA on increases in motilin and gastrin in this trial. Specifically, a nurse will collect a 10-mL blood sample, in which the serum will be separated using a centrifuge. The sample will be analyzed using both a Human Motilin ELISA kit and a Human Gastrin ELISA kit (Mybiosource Inc., San Diego, California, USA). This will be carried out at baseline and visit 12.

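### The repeated-measures group effect planned for the secondary outcomes will, in its ordinary layout, average in the pre-treatment value and so dilute a real treatment effect

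*Protocol article*

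**What the plan says.** Under Statistical analysis, Secondary outcomes, the Protocol article offers a repeated-measures ANOVA as one branch. For the other it says that "repeated measured ANCOVA will be used to analyze group-by-time interactions, as well as intergroup differences". Two results, the interaction and the group difference, are thus read from one model. The levels of the time factor are not given, and no covariate is named.

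The abstract gives the schedule: "the outcome will be evaluated at baseline, 3 weeks, and 6 weeks". Table 2 agrees for NDI-K, NRS, KGSRS, EQ-5D and PSS: baseline, V6, and the end visit (V13 in the table, visit 12 in the text). Gastrin and motilin have two measurements: "This will be carried out at baseline and visit 12". Cytokines and the two qi questionnaires follow the same two-point pattern.

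The section on baseline characteristics and homogeneity brings in ANCOVA only when the groups differ significantly at baseline. The Secondary outcomes section also plans a t test on NDI-K change after 6 weeks, with ANCOVA if there is a baseline covariate, and general two-sample t or Mann-Whitney comparisons.

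**The concern.** The hypothesis is that "Partially individualized EA treatment is superior to sham EA in terms of easing the symptoms of GERD". That concerns the state after treatment. A group-by-time interaction speaks to this only if baseline is among the times; with weeks 3 and 6 alone it would merely ask whether the effect changes between those two visits. So the natural layout has three time levels, one of them before treatment. The between-group effect of that model compares each patient's mean over all three. Randomisation makes the expected baseline difference zero, so a third of the average carries noise and no effect.

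At stake is a real difference at week 6 being reported as no difference between groups, while the same model's interaction may say otherwise. For NRS, KGSRS, EQ-5D and PSS the article does not say which of the listed tests is the treatment result.

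**Working it through.** **The plan's own figure.** The only planned size is for the primary outcome: "we assumed the PR would be 92.8 % in the treatment group and 57.1 % in the control group". With the pooled-variance formula, two-sided 0.05, 80% power and mean rate 0.7495:

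n = [1.960·√(2·0.7495·0.2505) + 0.8416·√(0.928·0.072 + 0.571·0.429)]² / 0.357² = 2.792 / 0.1274 = 21.9.

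This matches "the required sample size in each group was *n* = 21.9", and 21.9/0.75 = 29.2 supports 30 per group. No power, SD or correlation is given for any secondary outcome, so the rest uses assumptions.

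**Assumptions.** 30 per group; two-sided 0.05, as in the Statistical analysis section; SD 1 at every time; equal correlation ρ between times, 0.3 to 0.7; effect d = 0.73 SD at the end, chosen because an unadjusted end-value t test then has about 80% power. Two patterns over baseline, week 3 and week 6: building up (0, d/2, d) and full by week 3 (0, d, d).

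**What the group effect estimates.** With baseline as a level, it equals a two-sample t test on each patient's three-time mean.
- Full by week 3: (0 + d + d)/3 = 2d/3 = 0.487
- Building up: (0 + d/2 + d)/3 = d/2 = 0.365

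The variance of the three-time mean is (1 + 2ρ)/3. At ρ = 0.5 it is 0.667, so the standard error is √(2·0.667/30) = 0.211. The noncentrality is 0.365/0.211 = 1.73 or 0.487/0.211 = 2.31, on 58 degrees of freedom.

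**Comparators at ρ = 0.5.**
- End value, unadjusted: 0.73/√(2/30) = 2.83
- End value adjusted for baseline, residual variance 1 − ρ²: 0.73/√(2·0.75/30) = 3.26, on 57 degrees of freedom

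**Power from the noncentral t.**

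| Test | ρ = 0.3 | ρ = 0.5 | ρ = 0.7 |
|---|---|---|---|
| Group effect, building up | 48% | 40% | 34% |
| Group effect, full by week 3 | 72% | 62% | 54% |
| End value, unadjusted t | 79% | 79% | 79% |
| Change from baseline, t | 65% | 79% | 95% |
| End value, baseline-adjusted | 83% | 89% | 97% |

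Against the unadjusted end-value test, the group effect loses 31–45 points (building up) or 8–25 points (full by week 3).

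**Dilution alone.** To separate it from the gain of baseline adjustment, compare with the unadjusted mean of the two post-baseline visits, whose variance is (1 + ρ)/2. That has 73/67/62% (building up) and 93/89/85% (full by week 3). Averaging in baseline therefore costs about 26–28 or 21–31 points here. Over a wider grid (d 0.3 to 1.2, ρ 0.3 to 0.8, 22 or 30 per group) it costs about 1 to 32.

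**Very large effects.** At d = 1.2 with full effect by week 3, the group effect has 99/96/93% at ρ = 0.3/0.5/0.7, so little is lost. If the effect builds up it has 88/80/72%.

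**Chance imbalance.** Given a baseline gap b, each post-baseline difference shifts by ρb on average, so the group effect shifts by (1 + 2ρ)b/3. At ρ = 0.5, a one-standard-error gap (0.258) moves it by 0.172, which is 47% of 0.365. The same gap moves the unadjusted end value by 0.129, or 18% of 0.73. Baseline adjustment removes the shift on average.

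**Type I error.** In 40,000 simulated trials without effect, rejection was 4.9% for the group effect and 4.8% for the post-baseline mean.

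**The case against.** **The layout is inferred.** The article never says that baseline is a time level. Its ANCOVA branch could take baseline out of the response, and the phrase about group differences could mean contrasts at each visit. This stands as a limit: the point is conditional. But no covariate is named and adjustment depends on a significance test, so the unadjusted model remains the default.

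**Other tests cover the question.** The group-by-time interaction is not diluted in this way. At d = 0.8, ρ = 0.5 and full effect by week 3 it has 90% power, against 70% for the group effect and 86% for the week-6 change test. That is a substantial mitigation, though at ρ = 0.3 the interaction is no better (77% against 79%). The change test is named only for NDI-K, and none of these tests is baseline-adjusted by default.

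**This is detail for a fuller document.** A condensed article may leave coding of model terms to one. Here, however, the article does fix the model family, the results to be read from it and the condition for adjustment.

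**Stronger readings that a reader might infer.** One is that the group effect tests a wrong null. Under randomisation the expected baseline difference is zero, so the all-times mean difference is zero exactly when the post-baseline mean difference is, and type I error stays near 5%. Another is that the same model is prescribed for hormones, cytokines and the qi questionnaires. The article does not assign it to them; the general two-sample tests may be meant.

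**Conclusion.** The point holds, conditionally, for the five three-time secondary outcomes. If baseline is a time level, as the wording and the conditional ANCOVA rule make likely, the between-group effect is shrunk to two thirds or one half and takes in chance imbalance. The damage is to precision and power, not to validity under the null.

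A reader might take the power losses in the table as properties of this trial. They are not: they rest on an assumed 0.73 SD effect, assumed correlations, compound symmetry and 30 analysed per group. Part of the gap to the adjusted analysis is the ordinary gain from adjusting for baseline. What the documents support without those assumptions is the direction and, for each effect pattern, the degree of shrinkage. The primary responder analysis and the sample size are untouched.

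**What to change.** For NDI-K, NRS, KGSRS, EQ-5D and PSS:
- put only the mid-treatment and end visits in the repeated factor;
- always include the outcome's baseline value as covariate, not conditional on a significance test of baseline differences;
- report the group difference at the end visit, with its 95% confidence interval, as the between-group result;
- keep group-by-time as a description of the course.

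For outcomes measured only at baseline and end, name an ANCOVA of the end value on group and baseline.

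The cost is a rewording of the repeated-measures sentence and of the conditional ANCOVA rule, plus different model terms in the same software. It needs no new data, visits or participants.
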